#### **Adverse events (AE)**

To build a table with the frequency of AE per patient for each presented, as well as their severity, to studying which are the most frequent AE.

To study the relationship with the control variables and the appearance of each adverse reaction through a logistic regression analysis where the importance of each variable is obtained in the response prediction and the ratio of probability and conditional probabilities of response for each category of the qualitative variables and for the desired increments of the quantitative variables are estimated.

To compare both treatment groups considering the frequency of AE. For this purpose the chi-square test will be used. In case of quantitative variables that measure the intensity of a reaction, such as fever, blood pressure, ALT increase, etc. the Student's t test will be used, when possible. Otherwise, non parametric tests will be used. Paired tests will be used for the comparison between products and between periods of treatment.

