### **Design of the trial**

The population sample to be tested will be of 160 CHB patients, with variable serum transaminase levels, without treatment for at least 6 months, selected according to inclusion and exclusion criteria and allocated in two study groups (SG). The first study group, SG1 will include 80 CHB patients (HBeAg (+) and HBeAg (-)) that will be treated with 1 mL NASVAC (100 mcg per antigen, per dose per patient), administered in two cycles of inoculations, the first one by the intranasal route with five intranasal inoculations every 14 days each. During the second cycle patients will receive the same dosis (100 mcg per antigen) by the intranasal route and additionally the same dosis by the SC route,

The SG2 will be treated with Alpha-Interferon at standard dosis (weekly injection by SC route).

The treatment is discontinued for all patients of SG1 after completion of both cycles. The evaluation will continue during one year, but an interim report will be released after 5 and 10 administrations.

During the whole treatment period up to one year from the beginning of treatment, the systematic assessment of patients is launched to determine to what extent the treatment has driven them to generate the capacity to control the HBV load. This information is included in Figure 1.

[figure not shown]

**Figure 1.** General Algorithm of the trial

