#### **Evaluation criteria regarding safety**

All AE that appear during the study will be recorded in the Case Report Form of each individual.

All medical incidents that occur in the first hour after each administration of the vaccine, causally related or not with the vaccination will be recorded.

The rest of the observations will be evaluated in the follow up visits every 14 days.

The observation includes medical questionnaire of the patient, inspection of the injection site, axillary's temperature, and registration of all symptoms and signs referred by the patient. Explanation of how to act in case of abandonment or exit in the trial

The patients that abandon the trial will always be evaluated, except if the investigator loses contact with him. The information will be registered in the Case Report Form (CRF), including the cause of exit.

Quality control of the evaluation procedure

The clinical and laboratory evaluations will be preserved, in order to be examined by external quality controllers.

All primary data should be collected and conserved during the study.

The frequency of specific determinations as well as the type of determination per specific date according to the protocol are presented below: (Grey boxes: Determinations will not be performed).

| Test                    | Baseline
(not more than 2 months before starting treatment) | Week 12 | Week 24
EOT-V | Week 36 | Week 48
EOT-I | Week 72 | Week 96 | Reference Values
(M: male, F: female) |
|-------------------------|----------------------------------------------------------------|---------|------------------|---------|------------------|---------|---------|------------------------------------------|
| Hemoglobin              |                                                                |         |                  |         |                  |         |         | M: 12-17 g/dL
F: 11.5-15.5 g/dL       |
| Hematocrit (PCV)        |                                                                |         |                  |         |                  |         |         | 37-54%                                   |
| Leukocytes              |                                                                |         |                  |         |                  |         |         | 4-10 x 10  /L                |

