In addition, ALT and AST determinations will be conducted after each administration of NASVAC in the corresponding group in order to further study or explore any potential damage.

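### Paired tests are prescribed between two independent arms, and ALT increase is compared between arms although only the NASVAC arm has ALT measured after each dose

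*Protocol*

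**What the plan says.** Section 10 (Statistics), under Adverse events (AE), gives three instructions.

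- Frequencies: "To compare both treatment groups considering the frequency of AE. For this purpose the chi-square test will be used".
- Intensity variables: "such as fever, blood pressure, ALT increase, etc. the Student's t test will be used, when possible", with non-parametric tests otherwise. The sentence does not say whether the t test is paired.
- Then: "Paired tests will be used for the comparison between products and between periods of treatment".

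The products are NASVAC and interferon. Design of the trial and Treatment schedule assign NASVAC to SG1 and weekly pegylated interferon to SG2. No crossover and no matching is described. Under Evaluation of the biochemical status, paired analysis of transaminases is confined to change within each group, and the between-group comparison uses Student's t or Mann-Whitney.

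On sampling, section 7 has a common laboratory schedule with post-baseline columns at weeks 12, 24, 36, 48, 72 and 96. Below the table it adds that "ALT and AST determinations will be conducted after each administration of NASVAC in the corresponding group". No per-dose determination is stated for interferon.

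**The concern.** A paired test needs a defined partner for each observation. Two periods within one patient supply that; two different patients on two different products do not. An analyst following the clause would have to invent the pairing, for example by file order, and the p-value would change with the choice. With unequal arm sizes some patients would be left out.

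The ALT point is about ascertainment. The more often a patient is tested, the higher the largest recorded value and the greater the chance of at least one high value, whatever the treatment does. The NASVAC arm is tested more often by design, and ALT increase is named among the safety variables without saying which determinations enter the comparison.

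Both matter because the working hypothesis in section 2.7 expects fewer adverse reactions than with interferon, and the general objective includes widening the safety assessment.

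**Working it through.** The protocol gives no sample size, significance level or expected rate for the safety comparison, so there is no stated figure to reproduce.

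**1. Pairing independent arms**

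For n pairs with standard deviations of 1 and mean difference d, the paired statistic is t = d / √[(2 − 2r)/n], where r is the sample correlation between partners. In independent arms r is an accident of patient order.

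Inputs: n = 80 per arm (Design of the trial); d = 0.3 SD (assumed).

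- Unpaired: t = 0.3/√(2/80) = 1.897 on 158 df, p = 0.060.
- Random order gives r within about ±1.96/√79 = ±0.22.
- r = +0.22: t = 0.3/√(1.56/80) = 2.15 on 79 df, p = 0.035.
- r = −0.22: t = 0.3/√(2.44/80) = 1.72 on 79 df, p = 0.090.

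In 3,000 random pairings of one fixed data set, the central 95% of p-values was 0.034 to 0.089 and the full range 0.019 to 0.106.

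Long-run error is not harmed. In 20,000 simulated trials without a true difference, at nominal 5%, the paired test rejected in 4.9% (n = 60) and 4.8% (n = 80), the same as the unpaired test. Power at 0.4 SD was 57.4% paired versus 58.1% unpaired (n = 60) and 70.5% versus 70.8% (n = 80). The defect is a result that is not uniquely defined.

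**2. Unequal ALT sampling**

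Inputs from the protocol: ten NASVAC administrations (five in the first cycle; reports after 5 and 10), and common post-baseline columns at weeks 12, 24, 36 and 48 within the first year.

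Assumptions: ALT is taken at every listed visit (the table's shading is not readable in the text available); each value has probability p of exceeding some threshold; there is no true difference between arms.

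Determinations to week 24: NASVAC 10 + 2 = 12, interferon 2. To week 48: 10 + 4 = 14 versus 4.

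With independent values, P(at least one elevated) = 1 − (1 − p)^k:

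| Period | p | NASVAC | Interferon |
|---|---|---|---|
| Week 24 | 0.02 | 21.5% | 4.0% |
| Week 24 | 0.05 | 1 − 0.95^12 = 46.0% | 1 − 0.95^2 = 9.8% |
| Week 24 | 0.10 | 71.8% | 19.0% |
| Week 48 | 0.05 | 51.2% | 18.5% |

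ALT values within a patient are correlated, which shrinks the gap. Simulation at p = 0.05 to week 24, 80 per arm, chi-square at two-sided 5%:

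| Within-patient correlation | Ever elevated, NASVAC vs interferon | False-positive rate |
|---|---|---|
| 0 | 45.8% vs 9.6% | 99.95% |
| 0.5 | 27.0% vs 8.7% | 87% |
| 0.9 | 12.1% vs 6.8% | 20% |

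To week 48 the corresponding false-positive rates were 99.5%, 63% and 12%. A t test on each patient's highest value gave 58% to 100% to week 24 and 27% to 100% to week 48.

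With only the visits common to both arms and an unpaired test, the false-positive rate returned to 3.9%–5.3% (chi-square) and 4.1%–5.2% (t) across all correlations tried.

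**The case against.** **The paired clause may be a slip.** Frequencies are already assigned to chi-square, the biochemical section uses paired analysis only within groups, and paired tests between periods are legitimate. This stands and limits the damage. A reader might infer that all safety p-values are invalid, or that pairing unrelated patients inflates false positives. The documents do not support the first, because the chi-square comparison is untouched, and the simulation contradicts the second. The conflict with Student's t is also weaker than that with chi-square, since the t test is not specified as paired or unpaired.

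**No flare rate is defined.** A reader might infer that a biased flare comparison is already planned. The adverse-event section names ALT increase as a quantitative variable and sets no threshold, peak or ever-elevated endpoint; the biochemical section ties ALT to defined times. The choice of visits could be made in a statistical analysis plan that is not shown. This stands: the ALT point is a conditional risk, and the percentages illustrate one way of summarising the data.

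**The 12-versus-2 count is uncertain.** The resource table in section 12 budgets 8 ALT/AST determinations per patient (1,440 = 8 × 180), which does not fit ten post-dose tests plus scheduled visits. This also stands. The direction of the bias needs only that NASVAC patients are tested more often.

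**Common visits lose information.** Section 2.7 reports ALT peaks on NASVAC mainly in the first cycle. Five doses 14 days apart fall at weeks 0 to 8, before the first common post-baseline visit. This is a real cost of the fix.

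**First-hour events.** Section 7 requires recording of "All medical incidents that occur in the first hour after each administration of the vaccine", with no stated counterpart for interferon. A reader might infer that these events should also leave the comparison. That does not follow: the same section records all adverse events for every patient, and excluding them would discard NASVAC safety data.

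**Conclusion.** The paired clause is wrong as written for the comparison between products. No pairs exist, the p-value depends on an arbitrary order (0.019 to 0.106 in the example, against 0.060 unpaired), and the clause contradicts the chi-square instruction beside it and the within-group use elsewhere in section 10. Type I error remains nominal.

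The ALT point holds conditionally. Any peak, maximum-increase or ever-elevated comparison over all determinations would be biased against NASVAC. The illustration of 46% versus 10%, or 27% versus 9% at correlation 0.5, rests on the assumed 5% exceedance, ALT at every listed visit and no true difference. Because the bias runs against NASVAC, it could not produce a false claim that NASVAC is safer.

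The chi-square comparison of adverse-event frequency and the paired tests between treatment periods are unaffected. This concerns the safety analysis, not the main efficacy variable. It should be corrected.

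**What to change.** In section 10, Adverse events (AE), replace the paired-test sentence with:

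> Between products, use tests for independent groups (chi-square or Fisher; Student's t or Mann-Whitney). Use paired tests only within a group, between periods of treatment.

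Add that the between-group comparison of ALT/AST increase uses only visits scheduled in both groups, and that the NASVAC post-dose values are reported separately and descriptively. Keep first-hour events in the adverse-event data.

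The cost is wording. No visit or test changes, and post-dose monitoring stays as planned. The one analytical loss is that early post-dose ALT rises are described but not compared between groups.

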#### **Data center:**

The data processing and the statistical analysis will be performed by specialists of the Statistics Department of de Clinical Trials Division of the Center for Genetic Engineering and Biotechnology.

### **Number of patients**

The decision was to take 60 patients per group, 180 patients in total, considering the statistical hypothesis.

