### **Statistical hypothesis**

It is expected that the administration of NASVAC TVC, as defined in the present protocol, to chronic hepatitis B patients, will improve the specific anti-HBV immune response of treated patients and consequently will significantly increase the percentage of patients reducing the viral load to undetectable levels after treatment completion compared to the group administered with Pegylated Interferon, expecting a difference between groups of more than 20%.

H0: Equivalency in the percentage of chronic hepatitis B patients reducing the viral load to undetectable levels. Formally,  $H_0: \delta \leq \delta_0 = 0.20$  where  $\delta$  represents the difference between viral seronegativization, based in quantitative PCR assay with a sensitivity of 250 copies/mL, in the group treated with NASVAC compared to the group treated with Interferon.

H1: Superiority in the percentage of chronic hepatitis B patients reducing the viral load to undetectable levels. Formally,  $H_1: \delta > \delta_0 = 0.20$  where  $\delta$  represents the difference between viral seronegativization, based in quantitative PCR assay with a sensitivity of 250 copies/mL, in the group treated with NASVAC compared to the group treated with Interferon.

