### **Serology: Response:**

**HBeAg: Negativity:** disappearance from serum

**Seroconversion:** disappearance of HBeAg from serum and appearance of HBeAb.

**HBsAg: Negativity:** disappearance from serum

**Seroconversion:** Appearance of HBsAb in serum.

Both groups will be compared according to the categories defined above by the chi-square test or odds ratio calculation. A logistic regression will be also performed for a multivariate analysis of the influence of the different control variables that result significant in the previous univariate analysis. A signification level of  $p = 0.1$  will be considered. The potency will be of 80%.

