## 12. Assurance

### Necessary resources

| Resources for 80 patients            | Amount per patient        | Total                        | Responsible                                                          |
|--------------------------------------|---------------------------|------------------------------|----------------------------------------------------------------------|
| NASVAC                               | 30 bb 500mL               | 3000 bb of NASVAC            | CIGB                                                                 |
| IFN alpha 2b                         | 48 bb
considering 48 w | 4 000 bb
considering 48 w | CIGB                                                                 |
| HBV DNA quantitative*                | 4                         | 700 tests                    | Labaid
Dhaka

and
Hospital and
Faculty of
Medicine |
| Anti-HCV, and anti-HIV*              | 2 (each)                  | 360 tests                    |                                                                      |
| Liver function and hematology tests* | 5 (each)                  | 900 test                     |                                                                      |
| ALT, AST*                            | 8 (each)                  | 1440 test                    |                                                                      |
| HBV serology *                       | 5 (each)                  | 900 test                     |                                                                      |

(\*) A number of tests will be used before definitive recruiting (before day 0).

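### The sample-size sentence gives 60 patients per group and 180 in total for a two-group trial that the design section sets at 80 per group and 160 in total

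*Protocol*

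**What the plan says.** Protocol section 10, Number of patients: "The decision was to take 60 patients per group, 180 patients in total, considering the statistical hypothesis".

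Protocol section 4, Design of the trial: "The population sample to be tested will be of 160 CHB patients", divided between two study groups. "The first study group, SG1 will include 80 CHB patients", which leaves 160 − 80 = 80 for the second group, treated with interferon. The hypothesis, treatment, adverse-event and interim sections likewise describe only these two arms.

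Protocol sections 2.3 and 10, Statistical hypothesis: the sponsor is "expecting a difference between groups of more than 20" per cent in the proportion reaching undetectable HBV DNA. The formal hypotheses are δ ≤ 0.20 against δ > 0.20.

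Protocol section 10, Serology: Response: a significance level of 0.1 with no sidedness given, followed by "The potency will be of 80" per cent. Neither value appears in the primary-endpoint paragraphs.

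Protocol section 12, Necessary resources: the table is headed "Resources for 80 patients". It gives amounts per patient and totals, and a footnote to the laboratory rows says that some tests will be used before definitive recruitment.

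**The concern.** The sentence that fixes the size of the trial fails its own arithmetic for two groups and disagrees with the design section on both the group size and the total. These are enrolment targets, which an ethics committee approves and a site recruits to, so the conflict cannot be left to a later analysis plan. A team following one section would stop at a different number from a team following the other. The sentence also claims to rest on the statistical hypothesis, yet a reader cannot use that hypothesis to work out which number was meant.

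**Working it through.** **1. The plan's own figures.**
- Two groups of 60: 2 × 60 = 120, not 180.
- What 180 would require: 3 × 60 = 180 (three groups), or 180 / 2 = 90 per group.
- Section 4: 2 × 80 = 160, which is internally consistent.
- Spread: 180 − 160 = 20 between the two written totals, and 180 − 120 = 60 if the implied total is counted.

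An allowance for dropout does not bridge the gap. None is stated, and section 5.5 keeps every included patient in the analysis.

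**2. The resource table (section 12).** Dividing each total by the amount per patient:
- NASVAC: 3,000 / 30 = 100
- Interferon: 4,000 / 48 = 83.3 (80 patients would need 48 × 80 = 3,840)
- HBV DNA: 700 / 4 = 175
- Anti-HCV and anti-HIV: 360 / 2 = 180
- Liver function and haematology: 900 / 5 = 180
- ALT, AST: 1,440 / 8 = 180
- HBV serology: 900 / 5 = 180

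The heading and the interferon row fit about 80 per group. Four laboratory rows equal 180 patients, but these rows carry the pre-recruitment footnote, so 160 enrolled plus 20 screening sets would give the same totals. The table is compatible with either reading.

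**3. Power (illustrative).** The difference of 0.20, the level of 0.1 and the 80% power come from the protocol. Applying the last two to the primary comparison is an inference. The control rate is an assumption: section 2.4 mentions about 30% efficacy for current treatments on unspecified criteria, which is not a design input for this endpoint.

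Formula, null of no difference: power = Φ{[Δ − z·√(2p̄(1−p̄)/n)] / √[(p₁(1−p₁) + p₂(1−p₂))/n]}, where p̄ is the mean of the two rates.

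For 30% against 50% and n = 60: √(2 × 0.4 × 0.6 / 60) = 0.0894 and √((0.21 + 0.25) / 60) = 0.0876.
- Two-sided 0.10 (z = 1.645): (0.20 − 0.1471) / 0.0876 = 0.604, power 72.7%.
- One-sided 0.10 (z = 1.282): (0.20 − 0.1146) / 0.0876 = 0.975, power 83.5%.

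| Level | 60 per group | 80 per group | 90 per group | Needed for 80% |
|---|---|---|---|---|
| Two-sided 0.10 | 72.7% | 83.1% | 86.8% | 74 |
| One-sided 0.10 | 83.5% | 90.8% | 93.2% | 54 |

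Power at 60 per group over a range of control rates, difference 0.20:

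| Control rate | 5% | 10% | 15% | 20% | 30% | 40% | 50% |
|---|---|---|---|---|---|---|---|
| Two-sided 0.10 | 93.1% | 87.1% | 81.8% | 77.8% | 72.7% | 71.1% | 72.7% |
| One-sided 0.10 | 96.9% | 93.4% | 90.0% | 87.2% | 83.5% | 82.3% | 83.5% |

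**4. The hypothesis as literally written (null δ ≤ 0.20).** Power ≈ Φ[(δ − 0.20)/SE − z]. At a true difference of exactly 0.20 the first term is zero, so power equals alpha (10% at one-sided 0.10) at 60, 80 and 90 per group alike. For larger differences, with a 30% control rate, one-sided 0.10 and 80% power, z = 1.2816 + 0.8416 and z² = 4.508:
- δ = 0.30: (0.21 + 0.24) × 4.508 / 0.10² = 202.9, so 203 per group.
- δ = 0.40: (0.21 + 0.21) × 4.508 / 0.20² = 47.3, so 48 per group.

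The required size thus depends on a true difference that the protocol leaves open beyond exceeding 20%.

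**The case against.** The best defence is that section 4 states a coherent two-group design, the heading of the resource table agrees with it, and the section 10 sentence is a slip that nobody would recruit to. That has some force, and it supports 80 per group as the natural default. It does not remove the error: 180 recurs as a patient-equivalent in four laboratory rows, and the faulty sentence is the one that claims a statistical basis.

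Four stronger readings are tempting, and the documents do not support them.
- A reader might infer that 60 per group misses the protocol's 80% power. That requires a two-sided 0.10 level, a null of no difference and a control rate of about 20% or more. The protocol gives no sidedness and no control rate, and its alternative is one-sided. At one-sided 0.10, 60 per group exceeds 80% at every control rate tried.
- A reader might infer that no sample size can work under the stated null. That is true only if the true difference is exactly 0.20, and the protocol expects more.
- A reader might take the laboratory rows as proof of a second target of 180. The footnoted pre-recruitment tests could account for the excess over 160.
- A reader might suspect that the ambiguity allows stopping at a favourable total. Nothing in the protocol links recruitment to interim results, and the schedule puts the interim analysis in the last two months of the recruitment and treatment period.

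**Conclusion.** Wrong as written. In a two-group trial, 60 per group and 180 in total cannot both hold, and neither agrees with the 80 in the first group and 160 in total of section 4. This conclusion needs no assumption. The target is uncertain by 20 patients between the written totals, and by 60 if the implied 120 is counted.

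A loss of power is not established. It depends on a control rate and a sidedness that the protocol does not state: at 30% against 50% and a null of no difference, 60 per group falls short of 80% at two-sided 0.10 and passes at one-sided 0.10. Nor does the cited hypothesis identify the intended number.

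**What to change.** Replace the sentence under Number of patients with one target that agrees with section 4: 80 per group, 160 in total. If the sponsor intended another size, change section 4 to match.

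Beside the number, state the sponsor's own control rate, expected difference, null value, alpha and sidedness, and the power that results. The 30% and 50% used above are illustrations and should not be copied in as design values. A null of zero in particular would contradict the hypotheses in sections 2.3 and 10 unless those are revised too.

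In the resource table, show enrolled patients and screening allowance separately, so that the declared pre-recruitment tests are kept and the totals can be checked.

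The cost is one corrected sentence, a short statement of assumptions and a re-laid table. Keeping 160 adds no patients to the section 4 design. If 180 was the true intention, section 4 must rise by 20; if 120, it must fall by 40.
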